### Controls

All participants randomised to the control group will receive a prescription for spectacles at baseline, as is the standard of care in the area, and will receive near and/or distance spectacles at no cost at study closeout.

### Randomisation, allocation and masking

The randomisation sequence will be generated by the trial statistician in the LVPEI CTU using an online randomisation tool (https://www.sealedenvelope.com). Stratified randomisation will be done based on gender (male/female), age (below and above median), education level (below and above median), and baseline HMSE (below and above median). Group allocation will be concealed from the trial coordinator and field team until a potential participant is determined eligible. Trial personnel will not be masked to participants’ treatment assignment due to practical difficulties in assessing the main trial outcome without study spectacles being worn. Masking of participants with use of zero-power spectacles among controls is not considered ethical in this setting.

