**Methods:**

Cognitive Level Enhancement through Vision Exams and Refraction (CLEVER) is a single-centre, open-label, parallel-group, individually-randomised trial. Participants (760 total, 380 in each arm) aged ≥ 60 years with correctable vision impairment at distance and/or near (presenting visual acuity < 6/18 in the better-seeing eye and improving to > = 6/18 with spectacles and/or presenting near vision worse than N6 at 40 cm and improving to N6 with spectacles), normal hearing (able to repeat at least three out of six words whispered from a 50 cm distance in the better ear) and normal cognition (Hindi Mini-mental Status Examination score > 18/31) will be enrolled. After a comprehensive eye examination, intervention group participants will receive distance, near, or bifocal spectacles, while controls will receive a prescription and spectacles at the end of the trial. The primary outcome will be the three-year change in Longitudinal Aging Study in India–Diagnostic Assessment of Dementia (LASI DAD) global cognitive factor score, with and without adjustment for baseline score, age, gender, education and other potential confounders.

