### Inclusion

Age ≥ 60 years at the time of enumeration.Resident in the household for > = 3 months and planning to reside in the local area for the trial duration.Distance vision impairment (VI, presenting visual acuity [VA] < 6/18 in the better-seeing eye and improving to > = 6/18 with spectacles) and/or near VI (presenting near vision < N6 at 40 cm and improving to > = N6 with spectacles).Independent mobility with or without the support of a walking stick.Hindi Mini-mental Status Examination (HMSE) questionnaire score > 18 (out of 31) [19].Willingness to participate, to be randomised to either study group, and to adhere to the protocol.

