### Recruitment

Participants will be recruited through door-to-door household visits. Trained community eye health workers and social investigators will obtain written informed consent for preliminary screening after explaining study procedures. Each consenting participant will be assigned a unique identification number. The preliminary screening battery will include the following five components (Fig. 2):

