### Intervention

All participants in the intervention group will receive free near and/or distance spectacles plus instructions on their use within two weeks of the examination, with annual replacement in case of loss, breakage or change in power such that VA falls below the enrolment criteria. Adherence with use of spectacles will be assessed in both study groups through phone calls made every three months and half yearly home visits. Intervention group participants adherent with spectacle wear will be rewarded through nonfinancial incentives such as vouchers for diagnostic tests and other utility items at regular intervals. There will be no special criteria for discontinuing or modifying allocated interventions. No attempts will be made to prevent control participants from obtaining spectacles outside the study based on the prescriptions provided.

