## Data management and analysis plan

Data will be collected on paper forms initially and then entered into an electronic database developed in Microsoft Access (Microsoft Corporation, Redmond, Washington, USA) at the data centre at Gullapalli Pratibha Rao International Centre for Advancement of Rural Eye care in Hyderabad, Telangana, India. Data will be securely stored in encrypted cloud-based institute servers. Personal data will be stored in a different database with access restricted to primary investigators. Data will be analysed at the end of the trial when all follow-up assessments are completed. All randomised participants will be assessed based on the intention-to-treat principle in the main analysis. Per-protocol analysis will also be conducted as secondary analysis, analysing participants according to treatment they actually received. No formal interim analysis will be done for the primary outcome measure.

Baseline characteristics and follow-up measurements will be summarised as mean and standard deviation, median and inter-quartile range, or numbers and frequencies (%) as appropriate, depending on the scale and distribution of measurements. Histograms or Q-Q plots will be used to assess the normality of all continuous variables.

Global cognitive factor scores for our study population will be calculated using the cognitive test data from the LASI-DAD battery. This calculation is similar to that performed in the ACHIEVE trial, which investigated the impact of hearing aids on cognitive decline [33]. In ACHIEVE, the global cognitive factor score was the primary outcome measure calculated using the ARIC (Atherosclerosis Risk in Communities) cognitive battery [33]. The between-group difference in three-year change in LASI-DAD global cognitive score (primary outcome) will be calculated. A linear mixed-model regression analysis with restricted maximum likelihood estimation will be used to assess between-group differences in change in LASI-DAD global cognitive score over time after adjusting for potential confounders (baseline cognitive score, age, sex, education, visual function, quality of life, depression, falls, social interaction, and physical activity).

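### The primary analysis does not carry all four stratification factors: HMSE is not named in the adjusted model, and the version without adjustment drops every one

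*Protocol article*

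**What the plan says.** The section on randomisation, allocation and masking sets four two-level factors. One is gender, and the other three are split at a median: "age (below and above median), education level (below and above median), and baseline HMSE (below and above median". That makes 2 x 2 x 2 x 2 = 16 strata. No numeric cut-point is given, the population whose median is meant is not named, and a value equal to the median is not assigned to a side.

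The data management and analysis section fits a linear mixed model to the LASI-DAD global cognitive score "after adjusting for potential confounders (baseline cognitive score, age, sex, education, visual function, quality of life", followed by depression, falls, social interaction and physical activity. HMSE does not appear in that list.

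The Methods paragraph of the abstract defines the primary outcome as three-year change in the LASI-DAD score, "with and without adjustment for baseline score, age, gender, education and other potential confounders". Two versions of the primary result are therefore planned, and the article does not say which one is primary.

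**The concern.** Stratified allocation forces the arms to be nearly equal on the stratifying factors. Where those factors predict the outcome, the treatment difference varies less from one possible allocation to another than it would under simple randomisation. An analysis that leaves the factors out still counts the variance they explain as noise. Its standard error is then larger than the true sampling error, its confidence interval is too wide, and part of the precision gained by stratifying is lost.

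This matters here because age, education and a cognitive screening score are plausible predictors of cognition. The trial has gone to the trouble of stratifying on them and records all of them before allocation, so using them requires no new data.

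**Working it through.** **Stratifiers set against the analysis**

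| Stratifier | Adjusted mixed model | Version without adjustment |
|---|---|---|
| Gender | named (as sex) | absent |
| Age | named | absent |
| Education | named | absent |
| Baseline HMSE | not named | absent |

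The adjusted model does contain a baseline cognitive score. The abstract refers to the baseline score directly after naming the LASI-DAD outcome, so the natural reading is baseline LASI-DAD and not HMSE.

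**The plan's own figure.** Inputs from the sample size section: effect size 29% (read as 0.29 SD), two-sided 0.05, 90% power, 13% loss per year over three years.

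- Per arm, normal approximation: 2 x (1.960 + 1.282)² / 0.29² = 249.9, so 250.
- Retention: 0.87³ = 0.6585.
- Randomised: 250 / 0.6585 = 379.6, so 380 per arm and 760 in total.

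The stated 760 reproduces. It was sized for a two-sample t-test with no credit for covariates, so adding the stratifiers to the model does not alter it.

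**Size of the standard error effect.** Let R² be the share of outcome variance explained by the omitted stratifiers. With the arms balanced on them, the true variance of the treatment difference is proportional to 1 − R², while the unadjusted analysis reports one proportional to 1. The reported standard error is therefore too large by the factor 1/√(1 − R²), and the true two-sided error rate at a nominal 0.05 is 2 x [1 − Φ(1.96/√(1 − R²))]. The article gives no R², so these values are assumptions.

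| Case | Assumed R² | SE factor | True alpha |
|---|---|---|---|
| HMSE alone omitted, given baseline LASI-DAD | 1% | 1.005 | 0.049 |
| HMSE alone omitted, given baseline LASI-DAD | 5% | 1.026 | 0.044 |
| All four omitted | 10% | 1.054 | 0.039 |
| All four omitted | 20% | 1.118 | 0.028 |

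In the first two rows R² is the share of residual variance that HMSE explains beyond baseline LASI-DAD. Every row errs on the conservative side.

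**Does the unspecified median harm balance?** An illustrative simulation took 760 participants in 16 strata with blocks of 4, whole-point HMSE with mean 25 and SD 3, and half the participants without schooling. All of these except 760 and 16 are assumptions. The SD of the standardised difference between arms was:

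| Allocation | HMSE | Education | Age |
|---|---|---|---|
| Unstratified | 0.071 | 0.068 | 0.069 |
| Fixed cuts, ties below | 0.044 | 0.042 | 0.049 |
| Running median, ties below | 0.040 | 0.043 | 0.051 |
| Fixed cuts placed off the median | 0.046 | 0.032 | 0.046 |

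Any consistently applied cut gives most of the benefit.

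**The case against.** The strongest reply is that little is lost. The model set out in the analysis section already carries three of the four stratifiers. The fourth, HMSE, is a brief cognitive screen whose information largely overlaps with baseline LASI-DAD. The version without adjustment appears only in the abstract, beside the adjusted one. The 10% to 20% range has no source in the article, and for a change score it could be lower. The error costs precision and cannot produce a false positive. Most of this stands, and it limits the point to an improvement in precision. It does not remove it: the covariate list is explicit and leaves out a randomisation factor, and the unadjusted version is announced as one form of the primary result.

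A reader might go further and infer that the strata cannot be formed at all. Recruitment is door to door, allocation is released person by person ("Group allocation will be concealed from the trial coordinator and field team until a potential participant is determined eligible"), and spectacles follow within two weeks of the examination, so the medians of the final sample are not known at allocation. In addition, whole-point HMSE among eligible participants can take only the 13 values 19 to 31, so ties at the median are certain. The documents do not support that inference. The article never says that the median is that of the final sample, and an enumeration, a pilot of 20 people or outside data could supply a cut. A journal article may also leave numeric cuts and tie rules to the full protocol. Nor does it follow that balance is lost, because blocked allocation within any consistently applied cut still balances the arms, as the simulation shows.

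**Conclusion.** The point holds as a mismatch between the randomisation and the analysis. HMSE is not named in the adjusted model, and all four stratifiers are absent from the version without adjustment. For that version the standard error is about 5% to 12% too large if the stratifiers explain 10% to 20% of the variance in three-year change, and less if they explain less. For the adjusted model the loss is about 0.5% to 2.6%, on the assumption that HMSE explains 1% to 5% of the variance left after baseline LASI-DAD. Both errors are conservative, and the sample size calculation is sound.

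The unstated cut-points and tie rule are a matter of clarification only. They are no evidence that the stratification is unworkable or that it fails to balance the arms. Overall this is a modest improvement that costs nothing in data.

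**What to change.** In the analysis section, state that every version of the primary model includes gender, age, education and baseline HMSE. The result now described as unadjusted then becomes a minimally adjusted one. Age, education and HMSE may enter as continuous terms, which keeps information that a median split would discard. Name the adjusted model as primary.

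In the randomisation section, add the numeric cut-points for age, education and HMSE, where they came from, and that a value equal to the cut falls on the '<=' side. If randomisation has begun, report the cut-points and tie rule actually used. A median from the 20-person pilot would be imprecise (SE about 1.25 SD/√20 = 0.28 SD, or 0.8 HMSE points at an assumed SD of 3), so the enumeration or the cited LASI-DAD data would be a better source for cuts not yet set.

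The cost is one sentence in each section. All the variables are already collected, and neither the sample size nor the conduct of the trial changes.

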### Trial design

CLEVER is a single-centre, open-label, parallel-group, individually-randomised controlled trial, designed to test the impact of immediate versus delayed provision of free spectacles on rates of cognitive change among community-dwelling elderly persons.

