### Primary outcomes

Global cognitive factor scores, the primary outcome measure, will be calculated using cognitive test data from the LASI-DAD battery, administered at baseline, and 12, 24, and 36 months later. The LASI-DAD battery of cognitive and neuropsychological tests assesses several domains of cognitive function and has been validated for use in India, including in Telangana [25, 26].

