### Study team

A multidisciplinary team, including vision care professionals (ophthalmologist, optometrists and vision technicians), neuropsychologists and psychologists, social investigators, and community eye health workers will conduct this trial. The logistics of the trial, including appointments, management of the trial site, treatment allocation based on clinical trial unit (CTU) recommendation, and tracking of spectacles compliance, will be organized by a trial coordinator. The principal investigators ([name]) are responsible for the scientific and administrative aspects of the trial, with the support of the TMG.

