### Cognitive examination

The complete LASI-DAD neuropsychological test battery will be performed in the Telugu or Hindi languages. It assesses the following domains, 1) Orientation (Community Screening Instrument for Dementia); 2) visuospatial (constructional praxis); 3) language fluency (retrieval fluency); 4) immediate and delayed memory (word recall); 5) executive functions (Go-No-Go task); and 6) decision-making and judgment (judgement and problem-solving) [25, 26]. Psychologists will be trained to administer the cognitive test battery on patients and healthy older adults at the National Institute of Mental Health & Neuro Sciences (NIMHANS) under the supervision of the Clinical Psychologist/Neuropsychologist before performing the assessments on participants in the pilot and main trial.

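### The reason given for leaving all trial personnel unmasked does not require that the psychologists who administer the primary outcome know the arm

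*Protocol article*

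**What the plan says.** Under Trial design the article states that "CLEVER is a single-centre, open-label, parallel-group, individually-randomised controlled trial". Under Randomisation, allocation and masking it adds that "Trial personnel will not be masked to participants’ treatment assignment". No exception is made for outcome assessors. The reason given is "due to practical difficulties in assessing the main trial outcome without study spectacles being worn". Participants are unmasked on a separate ground: "Masking of participants with use of zero-power spectacles among controls is not considered ethical in this setting".

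On the outcome, Primary outcomes states: "Global cognitive factor scores, the primary outcome measure, will be calculated using cognitive test data from the LASI-DAD battery". Testing takes place at baseline and at 12, 24 and 36 months. Cognitive examination assigns administration of the battery to trained psychologists; it does not say who scores it.

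Two other statements bear on the point. On controls, Intervention says: "No attempts will be made to prevent control participants from obtaining spectacles outside the study based on the prescriptions provided". On who handles allocation, Study team says that "treatment allocation based on clinical trial unit (CTU) recommendation, and tracking of spectacles compliance, will be organized by a trial coordinator".

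**The concern.** The decision not to mask staff is stated positively and rests on one reason, so the reason can be tested against the decision. It concerns what the participant wears during testing. It says nothing about what the person giving the test needs to know. A psychologist can test a participant who has spectacles on without having been told why.

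The primary outcome is obtained face to face, by an examiner, on repeated occasions, in a trial where participants already know their arm. An examiner who also knows the arm can, without intending to, differ between arms in encouragement, prompting or time allowed. Any such difference goes straight into the between-arm contrast in cognitive change. Intention-to-treat analysis and covariate adjustment do not remove it, and nothing in the data would separate it from an effect of spectacles.

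**Working it through.** **Does the reason reach the decision?** Setting the sections side by side:

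- Randomisation, allocation and masking: the difficulty named is testing participants without spectacles on. This supports letting the tester see spectacles. It does not support telling the tester the allocation.
- Intervention and Controls: the intervention arm receives free spectacles. Controls receive a prescription at baseline and are free to fill it. Seeing spectacles therefore makes the intervention arm more likely but does not settle it. No control uptake rate is given, so the strength of the cue cannot be calculated.
- Study team: the trial coordinator already organises treatment allocation and the tracking of compliance. Withholding the arm from the psychologists needs no new role.
- Cognitive examination and Monitoring and quality control: the stated safeguards are supervised training, regular review of staff performance and periodic retraining. None of them concerns knowledge of the arm.

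**Reproducing the plan's sample size.** Inputs from Sample size: two-sided 0.05, 90% power, two-sample t-test, 13% loss per year, effect size 29%. The article gives no SD, so 29% is read as 0.29 SD (an assumption).

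- Completers per arm: 2 × (1.960 + 1.282)² / 0.29² = 250 after rounding up.
- Three-year retention: 0.87³ = 0.6585.
- Randomised per arm: 250 / 0.6585 = 379.7, so 380; total 760, as stated.

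**What an observer shift would do.** Let b be a shift in the final between-arm contrast of the global score, in SD units, with no true effect.

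- SE = √(2/250) = 0.0894 SD. The smallest significant difference is 1.96 × 0.0894 = 0.175 SD.
- Error rate = P(|Z + b/SE| > 1.96).
- b = 0.05: b/SE = 0.559; 0.081 + 0.006 = about 0.087, or 9%.
- b = 0.10: b/SE = 1.118; 0.200 + 0.001 = about 0.201, or 20%.

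As shares of the planned 0.29 SD, these shifts are 0.05/0.29 = 17% and 0.10/0.29 = 34%. Both values of b are chosen for illustration and come from no document.

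**The case against.** The strongest reply is that the trial is openly declared open-label, the lack of masking is disclosed, and a reason is given. Nothing is concealed or contradicted. That is right: the fault is a justification that falls short of the decision, together with a missing safeguard.

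A second reply is that masking the tester would often fail. Every intervention participant is supplied with spectacles, offered annual replacement where needed and rewarded for adherence, while controls get only a prescription until closeout. Participants know their arm and some will say so. This stands, and it limits the benefit. It does not show that testers must be told the allocation.

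A reader might infer more than the documents support:

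- **That the psychologists score the battery, and score it subjectively.** Who scores it is not stated. The domain listed as "decision-making and judgment (judgement and problem-solving" names the ability tested in the participant, not a method of scoring.
- **That bias would reach items needing no vision, such as oral word recall.** The mode of presentation is not given, and which items need no vision could only be guessed from the domain names.
- **That rater reliability for the cognitive battery is missing.** Inter-examiner reliability is mentioned only for visual acuity and refraction, but a condensed article may leave the cognitive part to the full protocol or a manual.
- **That rescoring from the paper forms would cure the problem.** It could not undo prompting or extra time during testing, and the article does not say that the forms record verbatim responses.
- **That only the coordinator and dispensing staff need know the arm.** Adherence is also followed by phone calls and home visits, and the article does not name the staff who make them.

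Training, performance review and retraining may reduce loose administration in general. They do not remove a difference between arms that comes from knowing the arm.

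**Conclusion.** The concern holds in a limited form. The blanket statement covers the psychologists who administer the primary outcome, and the one reason offered for it does not require that they know the allocation. Their inclusion follows from the general wording read with Cognitive examination; the masking section does not name them.

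The size of the problem is unknown. The figures of 9% and 20% are conditional. They assume 0.29 SD as the design effect, 250 completers per arm, no true effect, and a shift of 0.05 or 0.10 SD in the whole global score. A shift confined to a few tests would have to be larger on those tests to move the global score as far. The figures show that a bias well below the planned effect would matter. A reader might take them as the trial's expected false-positive rate; the documents do not support that, since they give neither size nor direction for any shift.

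This is an inexpensive improvement that should be made, not a defect that invalidates the design.

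**What to change.** Amend Randomisation, allocation and masking so that the statement on personnel no longer covers the LASI-DAD testers, and provide that:

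- testers are not told the arm and take no part in allocation, dispensing or adherence follow-up;
- the arm does not appear on the forms they use;
- participants are asked not to mention their arm during testing;
- the tester records a guess of the arm at each follow-up visit, so that the success of masking can be reported by arm.

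Participants can still be tested with spectacles on. Participants stay unmasked, and sample size, visits and treatment are unchanged.

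The cost is a protocol amendment through the approval route already described, a written procedure for testers, and one extra item on the follow-up form, all with existing staff. The downside is that masking will be partial, because spectacles are visible and some participants will disclose. The recorded guesses will show how far it succeeded.
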